### Interventions

#### Explanation for the choice of comparators

In this trial, no medication will be administered to the control group.

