#### Intervention description

A flowchart for enrolment and follow-up visits is shown in Fig 1. Written informed consent and provisional registration will be obtained from all participants. Within 8 weeks of provisional registration, baseline examinations will be performed, and participants will be registered based on the aforementioned inclusion and exclusion criteria. Eligible patients will then be randomized into two groups (group A, BBG9-1 group; group B, control group) using the minimization method. Among the background factors of the study participants, age (<65 years or ≥65 years), sex, and the abdominal symptoms (constipation or diarrhea) are used as allocation factors. Patients assigned to group A will receive probiotic BBG9-1 oral administration (Biofermin® tablets containing 12 mg of bifidobacteria, 2 tablets 3 times a day) along with their current treatment for 12 (± 3) weeks, and patients assigned to group B will continue the current treatment for 12 (± 3) weeks without probiotic BBG9-1 oral administration. Subsequently, the examinations, which are the same as the baseline examinations, will be performed 12 (± 3) weeks after the baseline examinations. For patients assigned to group A, the date of initiation of medication will be the starting date of observation for the study. For patients assigned to group B, the date of sampling at the baseline examination will be the starting date of observation for the study. Research patients who are not enrolled in the study will be excluded from participation at the time of their failure to enroll. Such cases will not be counted as the target number of cases to be enrolled in the study.

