### Statistical methods

#### Statistical methods for primary and secondary outcomes

Full analysis set (FAS) analysis will be performed for the primary and secondary endpoints. If necessary, per protocol set (PPS) analysis will be performed as a sensitivity analysis for the FAS analysis. In principle, the analysis should be performed at a two-sided significance level of 5%. The person responsible for the statistical analysis will prepare a separate statistical analysis plan that specifies the details of the statistical methods, including data handling. A statistical analysis plan will be prepared before the data are fixed. The primary endpoints will be treated as validation results, whereas the other endpoints will be treated as exploratory results.

The FAS will include the participants who are enrolled in the study and assigned to the study treatment. However, data on participants who violated the research protocol, such as enrolment without consent and registration outside the contract period, will be excluded. The PPS will include research participants who will be excluded from the FAS for the following reasons: violation of eligibility criteria, violation of exclusion criteria, violation of concomitant use of prohibited medications, and medication compliance rate > 120% or < 75%. The safety analysis set will include participants in whom research treatment has been initiated.

Summary statistics for the background data of study participants will be calculated for each group. Comparisons between groups will be made using the χ-square test or Fisher’s direct probability test for categorical variables and the two-sample t-test or Wilcoxon rank-sum test for continuous variables.

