The primary endpoints will be evaluated using analysis of covariance. A two-sample t-test will be performed for between-group comparisons and a one-sample t-test will be performed for within-group comparisons. The secondary endpoints will be evaluated using a two-sample t-test or one-sample t-test. For data without a normal distribution, the log-transformation will be attempted; however, if it does not improve the distribution, Wilcoxon rank-sum test or Wilcoxon signed-rank will be performed. For the Bristol scale score, between-group comparisons will be performed using the Wilcoxon rank-sum test, and within-group comparisons will be performed using the Wilcoxon signed-rank test. For percentage endpoints, the χ-square test or Fisher’s direct probability test will be performed. For safety, a list of all adverse events will be prepared for each group in the safety analysis population; if necessary, comparisons between groups will be made using Fisher’s direct probability test.

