Relevance to this study will be judged “not related” or “related” according to the following relevance criteria: the condition of the research participant; the time relationship with the treatment; the possibility of other factors.

A serious adverse event (SAE) is defined as any unwanted or unintended sign, symptom, or illness for a research participant, which is causally related to the research drug and corresponds to the following: 1) death, 2) life-threatening, 3) requires hospitalization or prolonged hospitalization for treatment, 4) results in permanent or significant disability or dysfunction, 5) the patient suffers from any other medically significant condition, 6) cases that are as serious as those listed in 1) to 5), and 7) congenital disease or abnormality in later generations.

If SAE occurs, the researchers will promptly take the necessary treatment, and regardless of the causal relationship between the SAE and the investigational drug in this study, the researchers shall report to the data center within 15 calendar days of becoming aware of the SAE, in accordance with the procedures of the institution. The data center will immediately summarize and report it to the administrator of the medical institution. The data center will immediately compile information, obtain instructions from the researchers, and report it to the research fund contributor (Biofermin Pharmaceutical Co., Ltd.). In the event of an adverse event other than an SAE, an adverse event will be noted in the CRF and reported to the data center upon submission of the CRF. The data center shall compile such information as appropriate, report it to the investigators and researchers, and receive corresponding instructions. The data center will also report the information to the research fund contributor (Biofermin Pharmaceutical Co., Ltd.), as appropriate. If new information concerning this research is obtained, the researchers will provide additional explanations to the participants and revise the consent and explanation documents as necessary.

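### The SAE definition requires a causal link to the drug, which the SAE reporting rule disclaims, and the safety set as worded omits the untreated control group

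*Protocol article*

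**What the plan says.** All references are to the protocol article.

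- **Safety set** (*Statistical methods for primary and secondary outcomes*): "The safety analysis set will include participants in whom research treatment has been initiated". The term for the treatment is not defined.
- **Control group** (*Explanation for the choice of comparators*): "In this trial, no medication will be administered to the control group". *Intervention description* adds that "patients assigned to group B will continue the current treatment for 12 (± 3) weeks without probiotic BBG9-1 oral administration".
- **Planned safety analysis** (*Statistical methods for primary and secondary outcomes*): "a list of all adverse events will be prepared for each group in the safety analysis population", with a between-group Fisher test if necessary. *Reporting of adverse events and harms* confirms that adverse events are analysed in this population.
- **SAE definition** (*Reporting of adverse events and harms*): an unwanted sign, symptom or illness "which is causally related to the research drug and corresponds to the following", followed by the usual seriousness criteria.
- **SAE reporting** (same section, next paragraph): report to the data center within 15 calendar days, "regardless of the causal relationship between the SAE and the investigational drug in this study". Any other adverse event goes on the CRF and is reported when the CRF is submitted.
- **Start of observation** (*Intervention description*): group A is observed from the day its tablets are started. The other arm has a different rule: "For patients assigned to group B, the date of sampling at the baseline examination will be the starting date of observation for the study".

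**The concern.** Seriousness and causality are separate attributes of an event. The protocol makes causality part of what an SAE is, and then writes a reporting rule that assumes it is not. Site staff following the definition would send a hospitalisation or death in a control participant, or one in group A judged unrelated, by the slower route. The trial is open-label, so whoever makes that judgement knows the allocation.

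The safety set has a related problem. Its criterion is the start of a treatment, and one of the two arms starts none. Harms are a declared outcome, and the control group is the only reference for telling background events from drug effects. A set that omits that group cannot support the tables planned in it.

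**Working it through.** **1. The plan's own figures.** Inputs from *Sample size*: difference 0.244, SD 0.412, alpha 0.05 (two-sided, per *Statistical methods*), power 0.80, ratio 1:1.

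n per group = 2 × (1.960 + 0.842)² × 0.412² / 0.244² = 2 × 7.849 × 0.16974 / 0.05954 ≈ 44.8, so 45. The t-based version gives 45.7, so 46. With 10% dropout, 45 / 0.90 = 50 per group and 100 in total. The stated numbers reproduce, and nothing below changes them.

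**2. SAE definition against reporting rule.** Take an event that meets a seriousness criterion, such as a hospitalisation.

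| Event | SAE under the definition? | Route as worded | Route the reporting rule intends |
|---|---|---|---|
| Group A, judged related | Yes | 15 calendar days | 15 calendar days |
| Group A, judged not related | No | With the CRF | 15 calendar days |
| Group B, any | No; never exposed | With the CRF | 15 calendar days |

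The clause setting causality aside can only matter in rows 2 and 3, and the definition has already removed both. It therefore has no effect.

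To show how often row 3 could arise, assume a serious event probability p per control participant over follow-up (the documents give none). The chance of at least one among 50 is 1 − (1 − p)^50:
- p = 1%: 0.395
- p = 2%: 0.636
- p = 5%: 0.923

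So the case is not remote, even at low assumed rates.

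**3. Safety set membership.**
- Group A: up to 50 qualify, on starting tablets.
- Group B: current treatment continues and no medication is given. *Intervention description* names an initiation date for group A only. On the plain wording, 0 qualify.

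With 50 against 0, the odds ratio is undefined and Fisher's p is trivially 1 whatever happens in group A. With both arms in the set, the test works. For assumed counts of k/50 against 0/50, the two-sided p is 2 × C(50,k) / C(100,k): 0.056 for k = 5 and 0.027 for k = 6.

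The full analysis set in the same section is defined by assignment, which covers both arms. The difficulty is specific to the safety set.

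**4. Start of counting.** Adverse events are recorded over the observation period. Randomisation follows the baseline examination, so observation in group B starts before allocation, and in group A at the first tablet. Follow-up is 12 (± 3) weeks after baseline in both arms. If g weeks separate baseline sampling from the first tablet, group A's window is shorter by g, or g/12 of the nominal period: about 8% for each week. The documents do not give g.

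**The case against.** The strongest reply is that the intended meaning is clear. The treatment named in the safety set is undefined, and the full analysis set sentence applies similar wording to both allocations. Listing events by group in the safety population makes sense only if controls belong to it. This stands as evidence of intent, but it does not rescue the wording: current treatment is continued, not initiated, and controls receive no medication. It shows that the definition, not the planned comparison, is the error.

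A reader might infer three stronger things, which the documents do not support.

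- **That the safety comparison is impossible.** The adverse event definition covers any unfavourable medical event in any participant, with no exposure or causality condition. Control data will exist, and a one-line definition makes them usable. The Fisher test is also only conditional.
- **That serious events may go unreported.** Events that are not SAEs still go to the data center with the CRF, which passes them on. What is lost is the SAE label and the 15-day route.
- **That the different observation starts bias the comparison.** The difference is real, but its size is not stated, the schedule figure is not shown, and the adverse event definition refers to the whole course of the study. No bias is demonstrated.

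A separate statistical analysis plan is promised and could restate the safety set. That does not remove the conflict in the article, and an analysis plan would not ordinarily govern the SAE definition or expedited reporting.

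**Conclusion.** The concern holds as two wording defects of practical consequence and one minor point.

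- **SAE rule:** an outright contradiction within one section. Read literally, every serious event in group B, and every one judged unrelated in group A, moves from 15-day reporting to reporting with the CRF.
- **Safety set:** on the plain wording it contains up to 50 of 100 participants, all in group A, and conflicts with the by-group analysis planned in it. This rests on taking the undefined treatment term to mean something newly started in the trial.
- **Start of counting:** the arms differ, by an amount the documents do not give.

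The different observation starts might suggest that the week-12 assessment also needs a new anchor. It does not: *Intervention description* and *Outcomes* already time it from the baseline examination in both arms. The primary endpoint and the sample size are untouched.

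**What to change.** 1. **SAE definition:** remove the condition of a causal relation to the research drug, leaving the seriousness criteria. Keep relatedness as the separate item already recorded and judged for adverse events, so no causality information is lost. The reporting rule then works as written.
2. **Safety set:** define it as group A participants who took at least one tablet plus all randomised group B participants.
3. **Counting window (minor):** state one common start date for counting adverse events in both arms. Leave the week-12 visit anchored to the baseline examination.

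The cost is a protocol wording change and possibly a few more expedited SAE reports. No extra participants or visits, and no change to the primary analysis, are needed.

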#### Outcomes

The primary endpoint of this trial will be the change in the total GSRS score from baseline to follow-up examination (12 ± 3 weeks after baseline examination). Secondary endpoints of this trial will be as follows: (1) change and percent change in following parameters from baseline to follow-up examination: GSRS subdomain scores, fecal properties/Bristol stool form scale, defecation frequency, blood test biomarkers (total bile acid, glycoalbumin, glucagon-like peptide-1, glucose-dependent insulinotropic polypeptide, glucagon, HbA1c, fasting plasma glucose, C-peptide, AST, ALT, gamma-glutamyltransferase, total cholesterol, high-density lipoprotein cholesterol, low-density lipoprotein cholesterol, triglycerides, blood urea nitrogen, and creatinine), physical examination (body weight and body mass index), urinary albumin creatinine ratio, gut microbiota (type of enterobacteria, relative abundance, alpha diversity, and beta diversity), macronutrients (total energy, carbohydrate, fat, protein, and dietary fiber intakes measured by brief-type self-administered diet history questionnaire [BDHQ]) [16]; (2) proportion of participants whose fecal property of Bristol stool form scale is within normal range (3.5–4.5); (3) medication adherence to the BBG9-1; (4) factors that affect GSRS total score or constipation/diarrhea subdomain scores; (5) stratification of following items by baseline symptoms (constipation/diarrhea): GSRS total score, GSRS subdomain scores, proportion of participants whose fecal properties are within normal range, defecation frequency, blood test biomarkers, and gut microbiota. The exploratory endpoints of this trial will be as follows: (1) blood, urine, and stool metabolomes (short, medium, and long chain fatty acids, amino acids, carbohydrates, and bile acids); (2) items other than nutrients evaluated in the secondary endpoints and items evaluated by the diabetes treatment satisfaction questionnaire (DTSQ) [17]; (3) items other than physical examination evaluated in the secondary endpoints; (4) items other than gut microbiota evaluated in the secondary endpoints; (5) change in lipopolysaccharide-binding protein; (6) subgroup analysis by age, sex, etc. Harm outcomes will also be evaluated based on various laboratory abnormalities and adverse reactions to the medication.

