#### Sample size

In a sub-analysis of a previous study [15,18], BBG9-1 oral administration changed the total GSRS score by -0.441 ± 0.499. In the non-treatment period, the change in the total GSRS score was -0.197 ± 0.314. Based on these findings, assuming a difference of 0.244 ± 0.412 in the change in GSRS between the two groups in the study, we obtained an alpha error of 0.05, a power of 0.80, and a sample size ratio of 1:1; 45 cases per group would be needed to detect a significant between-group difference. Dropouts with a dropout rate of 10%, 50 cases in one group, and 100 cases in both groups have been set as the target number of cases for this study.

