### Assignment of interventions: Allocation

#### Sequence generation

The investigators or researchers will enter the necessary information into the web system; if eligible, based on the GSRS score and the Bristol scale score, perform the main enrolment/assignment, and confirm the results. The participants will be assigned to group A or group B using the minimization method, with age, sex, and type of symptom (constipation or diarrhea) as allocation factors.

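### The single confirmatory endpoint is given both an ANCOVA and an unadjusted two-sample t-test between groups, and the protocol does not say which one decides

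*Protocol article*

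**What the plan says.** The Outcomes section defines one primary endpoint: "The primary endpoint of this trial will be the change in the total GSRS score from baseline to follow-up examination". The section on statistical methods for primary and secondary outcomes treats this endpoint as confirmatory and all others as exploratory, with a two-sided 5% level.

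On the method, that section says in two consecutive sentences: "The primary endpoints will be evaluated using analysis of covariance. A two-sample t-test will be performed for between-group comparisons". The second of these sentences goes on to plan a one-sample t-test within each group. Secondary endpoints then get a sentence of their own: "The secondary endpoints will be evaluated using a two-sample t-test or one-sample t-test". For non-normal data a log-transformation is to be tried, and a rank test used if that fails.

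Randomization is by minimization, "with age, sex, and type of symptom (constipation or diarrhea) as allocation factors". The Sample size section plans on a between-group difference of 0.244 with SD 0.412, giving 45 per group and 50 after dropout. It also gives the expected course without treatment: "In the non-treatment period, the change in the total GSRS score was -0.197 ± 0.314".

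A separate statistical analysis plan, to be written before the data are fixed, is to carry the details.

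**The concern.** Because the secondary endpoints have their own sentence, the t-tests in the sentence before it read as applying to the primary endpoint. On that reading the one confirmatory comparison has two tests, and they can disagree. The ANCOVA can remove chance imbalance in whatever covariates it includes. The t-test on change adjusts for neither baseline GSRS nor the minimization factors.

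Two things are at stake. If the reported test can be picked once both results are known, the nominal 5% no longer describes the procedure. If the t-test is taken as decisive, the precision available from baseline scores that are collected anyway goes unused.

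A separate, smaller matter is the one-sample test within each arm. The plan expects scores to fall without treatment, so a significant within-arm change says little about BBG9-1. The secondary endpoints likewise get t-tests on change although their baseline values are measured.

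**Working it through.** **Inputs from the protocol article.** Difference 0.244, SD of change 0.412, two-sided alpha 0.05, power 0.80, ratio 1:1, dropout 10%; untreated change -0.197, SD 0.314 (all from Sample size, with the two-sided level from the statistical methods section).

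**Assumptions, not in the article.** Baseline/follow-up correlation r, shown from 0.3 to 0.9; equal variances at both visits; baseline GSRS total score as the ANCOVA covariate.

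**1. The plan's own figure.** Per group, n = 2 × (1.960 + 0.842)² × (0.412 / 0.244)² = 2 × 7.85 × 2.851 ≈ 44.8, so 45. Then 45 / 0.90 = 50 per group. The stated figures reproduce, and this is the formula for an unadjusted two-sample comparison of change scores. With the t distribution, power at 45 per group is 79.3%.

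**2. Relation between the two tests.** Under the assumptions above, the variance of the ANCOVA estimate divided by that of the change-score estimate is (1 + r) / 2. The two test statistics have correlation √[(1 + r) / 2]. At r = 0.5, for example, the variance ratio is 0.75 and the correlation is 0.87. The statistics are close but not identical, so their rejection regions do not coincide.

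**3. Error rate and power.** Simulation with 45 per arm, SD of change 0.412, and 100,000 trials per setting:

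| r | Variance ratio | Type I error if either test counts | Power, t-test | Power, ANCOVA |
|---|---|---|---|---|
| 0.3 | 0.65 | 7.7% | 79.4% | 92.8% |
| 0.5 | 0.75 | 7.3% | 79.3% | 89.1% |
| 0.7 | 0.85 | 6.8% | 79.4% | 85.1% |
| 0.8 | 0.90 | 6.5% | 79.6% | 83.1% |
| 0.9 | 0.95 | 6.0% | 79.5% | 81.0% |

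Taken singly, each test had a simulated type I error between 4.9% and 5.1%. A bivariate normal calculation with the correlation in step 2 gives 7.8%, 7.3% and 6.8% at r = 0.3, 0.5 and 0.7, in agreement with the table. The ANCOVA here adjusts for baseline only; the three minimization factors are not simulated.

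**4. Within-group test in untreated controls.** The expected t is (0.197 / 0.314) × √45 = 0.627 × 6.708 ≈ 4.21. The noncentral t distribution gives 98.4% probability of significance at n = 45, and 99.2% at n = 50. This step uses only the plan's own figures.

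**The case against.** The strongest reply is that ANCOVA is named first and is the only method said to evaluate the primary endpoint, that an unadjusted t-test beside it is ordinary supportive reporting, and that details are expressly left to an analysis plan that is not shown. Part of this stands. That plan may already settle the ranking, and a covariate list is normally its business. It does not remove the problem in the text, because the protocol itself names two tests for one confirmatory comparison and sizes the trial on the second. The trial is also open-label, and the analysis plan is due only before data fixation, so the protocol wording matters. The sealed week-12 survey forms and the blinded data handling are real mitigation.

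A reader might go further and infer any of the following, which the article does not support:

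- *The 5% level is already lost.* Nothing says that significance on either test counts as success. The inflation is conditional on that.
- *Power falls short of plan.* The trial was sized on the unadjusted comparison, so the t-test delivers about the planned 80%. What would be forgone is the extra power from adjustment, which is small if r is near 0.9.
- *The within-group tests add to the error rate.* They leave the between-group error rate unchanged, and the article nowhere makes them a success criterion. The sample size is set for a between-group difference, and the lack of a control group is named as the weakness of the earlier work.
- *Entry on a GSRS subdomain score of at least 3 explains the untreated fall.* The article does not say how the patients behind that figure were selected, and the endpoint is the total score, not the subdomain score.

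For the secondary endpoints, t-tests on change are valid under randomization and those endpoints are exploratory. Baseline adjustment there is an improvement, not the correction of an error.

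**Conclusion.** The point holds as a failure to name the decisive test for the single confirmatory endpoint. Its consequences are conditional: type I error of about 6% to 8% if either test may be quoted, and power of about 79% in place of about 81% to 93% if the t-test decides. Both ranges rest on an assumed r from 0.9 to 0.3, equal variances at both visits, and baseline GSRS as covariate. The finding that within-group significance cannot support efficacy (about 98% in untreated controls) needs only the planning figures, but it concerns interpretation and not error control.

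**What to change.** - State that the sole confirmatory analysis is one ANCOVA of change in GSRS total score, with arm, baseline GSRS total score, age group, sex and symptom type, at two-sided 5%.
- Label the two-sample t-test on the primary endpoint an unadjusted sensitivity analysis.
- State that within-group changes are descriptive and support no efficacy claim.
- As a free improvement, use baseline-adjusted ANCOVA in place of t-tests on change for continuous secondary endpoints that are approximately normal, or become so after log-transformation. Keep the rank-test fallback for the rest.

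The cost is a few sentences, to be settled before the data are fixed. No new data are needed, and 45 evaluable per group (50 enrolled) remains sufficient. The four covariates use 4 degrees of freedom: with 90 evaluable patients the residual falls from 90 - 2 = 88 to 90 - 6 = 84.

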### Eligibility criteria

Patients must satisfy all of the following inclusion criteria. The inclusion criteria are as follows: (1) symptoms of diarrhea or constipation; (2) three or higher in Gastrointestinal Symptom Rating Scale (GSRS) subdomain score (diarrhea or constipation); (3) T2DM patients without diabetic polyneuropathy; (4) no new antibiotic usage within 12 weeks prior to consent; (5) no new diet interventions within 12 weeks prior to consent; (6) no changes in medications which can affect gastrointestinal symptoms and microbiome (addition or discontinuation of medications or change in use or dosage of medications) within 12 weeks prior to consent; (7) aged 20 and up and under 75 years or less at the time of consent; (8) written consent obtained from the individual. The exclusion criteria are as follows: patients with (1) mean defecation frequency < 1 or > 42 times/ week within 4 weeks before giving their consent; (2) structural diseases, including inflammatory diseases (infectious enteritis, diverticulitis, Crohn’s disease, and ulcerative colitis), and stenotic lesions, diagnosed by colonoscopy within 5 years before giving their consent; (3) having both ≥ 3 on the GSRS constipation subscale and > 4 on the Bristol stool scale; (4) having both ≥ 3 on the GSRS diarrhea subscale and < 4 on the Bristol stool scale; (5) gastrointestinal symptoms of both diarrhea and constipation; (6) past history of inflammatory bowel disease and celiac disease; (7) HbA1c level ≥ 9% at the time of consent; (8) use of alpha-glucosidase inhibitors within 4 weeks prior to consent; (9) cerebral infarction, stroke, or myocardial infarction within 12 weeks prior to consent; (10) severe hepatic dysfunction defined as alanine aminotransferase (ALT) or aspartate transaminase (AST) level 5 times equal or higher than the upper normal limit; (11) severe renal dysfunction defined as estimated glomerular filtration rate < 30 mL/min/1.73 m^2^; (12) active malignant tumor; (13) allergy history of bifidobacteria; (14) usage of any other supplements or medications that affect intestinal function; (15) usage of medications that are likely to cause abdominal symptoms (e.g., gastroprokinetic agents, drugs for dyspepsia, antiemetic agents, laxatives, and anticholinergics); (16) patients with changes in diet within 12 weeks prior to consent; (17) other conditions that the researcher or investigator thinks inappropriate for the study.

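### Pooled tests of continuous secondary endpoints use neither the minimisation factors nor the baseline value as covariates, which costs precision, mainly for the GSRS diarrhea and constipation subdomains

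*Protocol article*

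**What the plan says.** Under Sequence generation, patients are assigned "using the minimization method, with age, sex, and type of symptom (constipation or diarrhea) as allocation factors"; Intervention description gives the age cut as 65 years. Under Outcomes, the secondary endpoints open with "change and percent change in following parameters from baseline to follow-up examination: GSRS subdomain scores" and go on to defecation frequency, blood biomarkers, body weight, nutrients and others.

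The statistical methods section gives the primary endpoint an analysis of covariance. For the rest it states: "The secondary endpoints will be evaluated using a two-sample t-test or one-sample t-test". Log-transformation or Wilcoxon tests are the fallback for non-normal data. No covariate or stratification factor is named for any pooled between-group test of a secondary endpoint.

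Three other statements bear on the point. All endpoints other than the primary are declared exploratory. Secondary endpoint (5) and the section on additional analyses provide results by baseline symptom. Details of method are left to a separate analysis plan.

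**The concern.** Minimisation makes the arms nearly equal in symptom type, age group and sex, so differences between those groups hardly enter the treatment comparison. A plain t-test still counts them as random noise. Its standard error is then larger than the real sampling error, its intervals are too wide and it rejects a true null less often than 5%. The change score subtracts the baseline value but does not adjust for it, so predictable variation linked to baseline also stays in the error term.

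The subdomain scores are where this most plausibly matters. Entry requires "three or higher in Gastrointestinal Symptom Rating Scale (GSRS) subdomain score (diarrhea or constipation"), and patients with both symptoms are excluded. The pooled sample for the constipation subdomain is therefore one group selected for high scores and one that was not, and the diarrhea subdomain mirrors it. Regression to the mean and room to improve would make expected change differ between the two. Defecation frequency may behave similarly. At stake is precision on outcomes close to the trial's stated objective, from data that are collected anyway.

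**Working it through.** **The plan's own figure.** The Sample size section is "assuming a difference of 0.244 ± 0.412 in the change in GSRS between the two groups in the study", with "an alpha error of 0.05, a power of 0.80, and a sample size ratio of 1:1". The standardised difference is 0.244/0.412 = 0.592, so n = 2 × (1.96 + 0.8416)² / 0.592² ≈ 44.8, i.e. 45 per arm, and 45/0.9 = 50. Both stated figures reproduce. They concern the primary endpoint only; no figure is given for any secondary endpoint. About 90 evaluable patients are used below.

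**General effect of omitted covariates.** Let R² be the share of change-score variance explained by baseline and the minimisation factors. Adjustment multiplies the SE by √(1 − R²). If the arms are balanced on what R² measures, the unadjusted test's real type I error is 2[1 − Φ(1.96/√(1 − R²))]. For an endpoint with 80% unadjusted power at 45 per arm:

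| R² | SE factor with adjustment | Power with adjustment | Real type I error, unadjusted |
|---|---|---|---|
| 0.1 | 0.95 | 0.84 | 3.9% |
| 0.2 | 0.89 | 0.88 | 2.8% |
| 0.3 | 0.84 | 0.92 | 1.9% |
| 0.4 | 0.77 | 0.95 | 1.1% |

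For the baseline value alone, with equal variances and baseline–follow-up correlation r, R² = (1 − r)/2. Taking r = 0.8, 0.5 and 0.3 gives power 0.84, 0.90 and 0.94. Neither R² nor r is in the documents, so these are ranges.

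**A subdomain, by symptom type.** Assumptions: half the sample constipation, within-type SD 1, and mean change differing by D between types.
- Total variance is 1 + D²/4. The SE reported by the t-test is (2/√90) × √(1 + D²/4) = 0.211 × √(1 + D²/4), while the real SE under balance is 0.211.
- At D = 1.0 the reported SE is 0.236. At D = 1.5 it is 0.264.
- Type I error by the formula at D = 0.5, 1.0, 1.5: 4.3%, 2.8%, 1.4%.
- Simulation (3000 trials per scenario, three-factor minimisation with an 80% biased coin): 4.7%, 2.7%, 1.5%. Mean reported against true SE was 0.236 against 0.212 at D = 1.0 (11% too large). At D = 1.5 repeat runs put the excess at 19% to 23%. The adjusted model stays near 5%.

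**Power with an effect of 1.1 SD confined to the qualifying half** (pooled effect 1.1/2 = 0.55). For the t-test at D = 1.0, the treated-arm variance is 1 + 2.1²/4 = 2.10 and the control-arm variance 1.25, mean 1.68. The reported SE is 0.211 × √1.68 = 0.273, and power is Φ[(0.55 − 1.96 × 0.273)/0.211] ≈ 0.53. Simulated results:

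| D | Pooled t-test | Pooled, adjusted for the factors |
|---|---|---|
| 0.5 | 62% | about 70% |
| 1.0 | 52% | about 70% |
| 1.5 | 38% | about 70% |

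**The by-symptom comparison already planned, same scenario.** In the qualifying half there are 22 to 23 patients per arm, with SE √(2/22.5) = 0.298 and 1.1/0.298 = 3.69. Noncentral-t power is about 95% whatever D is, and about 90% at half the alpha.

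**The same average effect spread over both types** (0.55 SD in each). Pooled t-test power is Φ[(0.55 − 1.96 × 0.211√(1 + D²/4))/0.211] = 72%, 66%, 56% at D = 0.5, 1.0, 1.5. With adjustment it is Φ(0.55/0.211 − 1.96) ≈ 74%. A single by-symptom test has about 44%. Here adjusting the pooled test is what helps.

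**The case against.** The strongest reply is that a reader might infer that the trial will miss real effects on the two subdomains closest to its question. The documents do not support that. The by-symptom comparison is a listed secondary endpoint, removes the between-type difference entirely, and in the confined-effect scenario has about 95% power, above even the adjusted pooled model. This stands. It does not carry over to an effect shared by both symptom types, and no baseline adjustment is named for those analyses either.

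A reader might also infer an equal loss across all secondary endpoints. Nothing in the documents shows that age, sex or symptom type predicts change in lipids, creatinine, weight or nutrient intake. The symptom-type argument reaches the two subdomains and perhaps defecation frequency. Elsewhere any gain would come mainly from the baseline value and is unquantified.

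Three further replies hold in part:
- The endpoints are exploratory, and no sample size rests on them. This lowers the importance.
- The error is conservative: no bias and no excess of false positives.
- The size depends on assumptions. At D = 0.5 type I error is close to nominal, and at D = 0 adding symptom type alone leaves the null SE unchanged.

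The separate analysis plan may add adjusted analyses. That does not remove an unadjusted test which the article names for these endpoints while giving the primary endpoint a different method.

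**Conclusion.** The point holds for the pooled between-group tests of continuous secondary endpoints, chiefly the GSRS diarrhea and constipation subdomains. Where symptom type or baseline predicts change, the stated t-test is conservative and inefficient. Over the assumed range D = 0.5 to 1.5, type I error falls to about 4.7% to 1.5%, and pooled power is about 62% to 38% against about 70% for a 1.1 SD effect in the qualifying half. The direction follows from the design; the size rests on D, an even symptom split and 90 evaluable patients, and D and the split are not in the documents. It does not amount to biased estimates, inflated false positives or a general failure to detect effects, and the primary sample size is untouched. Importance is modest.

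**What to change.** In the statistical methods section, for between-group comparisons of continuous secondary endpoints, replace the two-sample t-test with analysis of covariance of the change. Include arm, the endpoint's own baseline value, symptom type, age group (<65/≥65) and sex, and report the adjusted difference with its 95% CI. Where normality fails even after transformation, use a rank test stratified by symptom type instead of the plain rank-sum test. In the by-symptom analyses, adjust for the baseline value.

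The cost is wording, settled before the data are fixed. No new data or patients are needed. The four extra terms use four of about 88 degrees of freedom (90 − 2), leaving about 84.
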